### **Section 3: Trial Objectives and Purpose (general statement)**

Primary objective and secondary objectives: Deliver to the treating team a deprescribing opportunities report prior to the participant's hospital discharge to facilitate deprescribing. It is hypothesized that the intervention will lead to a reduction in Adverse Drug Events within 30 days post-discharge through the cessation of PIMs. Secondary outcomes will include adverse events at 30 days post hospital discharge as well as number of other measures listed subsequently.

## Section 4: Trial Design

*4.1 A specific statement of the primary endpoints and the secondary endpoints, if any, to be measured during the trial.*

*Primary outcome:* Any adverse drug event within 30-days of hospital discharge (as defined by a 5 or 6 on the Leape and Bates scale). ADEs could include adverse drug withdrawal events (ADWEs).

*Secondary outcomes:*

- Proportion of patients with one or more PIM discontinued at discharge
- Absolute number of medications at discharge
- Absolute number of PIMs at discharge
- Adverse drug withdrawal events within 30-days post discharge
- Absolute number of medications at 30 days post-discharge
  - Proportion of medications that remain deprescribed at 30 days post-discharge
- Adverse events within 30-days post discharge
  - 30-day readmissions (ER or hospitalization) within 30-days post discharge
  - 30-day mortality in those that survive to hospital discharge
  - Falls within 30-days of hospital discharge
- 30-day post-discharge sleep questionnaire responses
- 30-day self-reported health-related quality of life

*Sensitivity analyses:*

- Adverse drug events as defined by a 4,5 or 6 on the Leape and Bates scale

*Effect by:*

- Biological sex
- Admission from a long-term care home
- Palliative status
- Frailty status (dichotomized as moderate to severely frail vs not)

*4.2 A description of the type/design of trial to be conducted (e.g., double-blind, placebo-controlled, parallel design) and a schematic diagram of trial design, procedures, and stages.*

This is a cluster randomized trial comprising 3 clusters: Quebec, Ontario, and Western Canada (Alberta and British Columbia).

*4.3 A description of the measures taken to minimize/avoid bias, including:*

(a) Randomization

The order that the cluster enters intervention is randomized prior to the start of the study.

(b) Blinding and Allocation Concealment

Study sites will only learn that they are crossing over to the intervention 4 weeks prior.

Healthcare personnel and patients at participating sites will remain blinded to the specific objectives of the study while in the control phase. They will be aware that we are conducting a study of post-discharge adverse events; however, they will not know that we are specifically looking at medication appropriateness, deprescribing, and adverse drug events. When study sites cross into intervention it will no longer be possible to blind them to the objectives.

Adjudication of adverse events and adverse drug events is blinded and independent (the adjudicator does not know if the participant is in the intervention or the control phase of the trial). Adjudication only begins halfway through the second cluster entering intervention such that a significant proportion of participants are in intervention and control, thus minimizing the ability of the adjudicator to “guess” the intervention status.

Adjudication files are stripped of name of province, institution, hospital, doctors, and all specific dates (only relative dates are used). The patient file contains no identifiers and only a scrambled patient ID with randomly generated letters and numbers. Files from French hospitals and interviews will be fully translated to English prior to adjudication by personnel independent of the adjudication. Adjudications are randomly distributed to adjudicators using a computer-generated algorithm and are performed in duplicate. Where there is disagreement between reviews in terms of presence of an adverse event or adverse drug event, a 3rd independent blinded adjudicator will be randomly assigned. That adjudicator will not know they are performing a third review. We use agreement by 2 persons to constitute adverse drug events and adverse events.

4.4. The expected duration of subject participation, and a description of the sequence and duration of all trial periods, including follow-up, if any.

|                                                                             | Day 0 | Day 1-2 | Day 2-3 | Day 4 | Day 5 to Day TBD | Day of D/C | Day of D/C +28- 35 Days | Day of D/C + >35 Days |
|-----------------------------------------------------------------------------|--------------|----------------|----------------|--------------|-------------------------|-------------------|--------------------------------|---------------------------------|
| Hospital admission                                                   | X     |                |                |              |                         |                   |                                |                                 |
| Medication reconciliation                                            | X     | X       |                |              |                         |                   |                                |                                 |
| Patient consent                                                      |              | X       | X       |              |                         |                   |                                |                                 |
| Enter data for MedSafer report (medical history and medication list) |              | X       | X       |              |                         |                   |                                |                                 |
| Provide MedSafer report to team                                      |              | X       | X       | X     |                         |                   |                                |                                 |
| Team acts on recommendations                                         |              | X       | X       | X     | X                | X          |                                |                                 |
| Hospital discharge                                                   |              |                |                |              |                         | X          |                                |                                 |
| Discharge medication data collected                                  |              |                |                |              |                         | X          |                                |                                 |
| 30-day follow-up phone interview                                     |              |                |                |              |                         |                   | X                       |                                 |
| Adjudication of file                                                 |              |                |                |              |                         |                   |                                | X                        |

Study diagrams:

[figure not shown]

\*\*Study diagram updated from 6 clusters to 3 clusters (changed prior to first 200 patients)

Cluster randomized flow diagram: (updated to reflect 3 clusters instead of 6 prior to first 200 patients)

[figure not shown]

380 *4.5 A description of the "stopping rules" or "discontinuation criteria" for individual subjects,*  
381 *parts of trial and entire trial.*  
382

383 Given the trial design (cluster-randomized) and to keep the case files blinded to intervention  
384 status, adjudication of the primary outcome will be delayed until sufficient time has passed with  
385 multiple groups in the intervention phase. Given the trial design and the need for duplicate  
386 reviews, it is not possible to have early stopping rules. The trial will complete enrolment. As the  
387 intervention is considered low risk and best practice, it is not expected that there will be serious  
388 adverse events linked to the intervention necessitating early stopping.  
389  
390

## Section 5 – Selection and Withdrawal of Subjects

### *5.1 Subject identification and inclusion criteria.*

#### *5.1.a Specific inclusion criteria:*

Participants eligible for this study include patients who are i) aged 65 years or older; ii) taking 5 or more medications; and iii) admitted to the study units.

#### *5.1.b Subject exclusion criteria:*

- Expected to die within 1-3 months
- Patient or proxy do not speak English or French
- Did not provide consent
- No provincial health insurance
- Will be unable to reach by telephone post-discharge
- Taking fewer than five usual home medications
- Admission or transfer to a non-study unit is expected: patients who are ultimately discharged from non-study units during their hospitalization will be excluded unless that unit is a transitional care, rehabilitation, or post-acute care unit used to bridge the gap between acute medical hospitalization and community services. For example, patients transferred to and subsequently discharged from a surgical unit (where there is no intervention) will be excluded.

### *5.2 When and how to withdraw subjects from the trial:*

Withdrawal by participant: Participants will be able to withdraw from the study at any time upon request without penalty. Should participants discontinue, we will request that data accrued to date be retained for analysis but will terminate future follow up. We will also request permission to confirm ER visit, hospitalization, and vital status at day 30 post-hospital discharge.

Withdrawal by investigator: If any clinical adverse event (AE), laboratory abnormality, or other medical condition or situation occurs such that continued participation in the study would not be in the best interest of the participant or interferes with the integrity of the study data. If the participant meets an exclusion criterion (either newly developed or not previously recognized) that precludes further study participation.

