### *5.3 The type and timing of the data to be collected for withdrawn subjects.*

Vital status and hospitalization at 30-days post hospital discharge

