## Section 9 – Statistics/Statistical Analysis Plan

### 9.1a *A description of the statistical methods to be employed, including timing of any planned interim analysis(es).*

Baseline characteristics will be expressed as numbers and percentages for categorical variables and median and interquartile range (IQR) for continuous variables. Differences between control and intervention baseline characteristics will be compared by chi-square or rank-sum as appropriate (for descriptive purposes since this is a cluster randomized trial and there may be chance imbalances due to case-mix during the intervention and control periods).

All analysis will be by intention to treat except where otherwise noted.

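### Section 5.2 lets investigators who know the phase withdraw participants for exclusion criteria that arise after enrolment, and withdrawal costs the ADE outcome; the bias is of unknown size and direction and may be small

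*Protocol*

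**What the plan says.** Section 5.2 of the protocol gives the investigator two grounds for withdrawing a participant.

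- The first begins "If any clinical adverse event (AE), laboratory abnormality, or other medical condition or situation occurs". It applies only if staying in the study would be against the participant's best interest or would compromise the study data.
- The second is "If the participant meets an exclusion criterion (either newly developed or not previously recognized) that precludes further study participation".

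The exclusion list in 5.1.b includes "Expected to die within 1-3 months", "Taking fewer than five usual home medications" and inability to be reached by telephone after discharge. It also states that "patients who are ultimately discharged from non-study units during their hospitalization will be excluded unless that unit is a transitional care" or a similar bridging unit.

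For withdrawn subjects, 5.3 lists only "Vital status and hospitalization at 30-days post hospital discharge". Section 5.5 adds emergency visits and describes a two-minute call, made if the person agrees. Sections 6.1 and 7.2 make the structured 30-day interview the basis of the record from which ADEs are adjudicated.

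In 9.1a the general rule is "All analysis will be by intention to treat except where otherwise noted". The primary model is then limited to patients who agreed to and took part in follow-up after discharge. Section 9.7 describes the primary set differently, as consenting subjects who received a report and survived to discharge, and does not mention withdrawal. Section 4.3(b) accepts that sites cannot be kept blind to the objectives once they cross over.

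**The concern.** Eligibility should be settled on information that predates exposure. If a criterion can be met later and then used to end participation, the patients who reach the outcome assessment are selected partly by what happened after the report was delivered. The person applying the rule knows the phase. Section 2.6 leaves prognosis to the treating team, and that team receives the report in the intervention phase (2.5).

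Two results are exposed. One is the primary comparison of 30-day ADEs. The other is the number of adverse drug withdrawal events, which sections 8.1 and 9.1a treat as the safety signal of deprescribing. A patient who deteriorates, is judged to have a short prognosis and is withdrawn before the interview contributes to neither. The blinded, duplicate adjudication in 4.3 cannot correct this, because it sees only the files that reach it.

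**Working it through.** **1. Does withdrawal remove the primary outcome?** Set side by side:

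- 5.2 permits withdrawal on a criterion that first arises after enrolment.
- 5.3 and 5.5 then leave vital status, hospital use and emergency visits, with agreement.
- 6.1 and 7.2 take the ADE record from the 30-day interview.
- 9.1a restricts the primary model to follow-up participants.

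A patient withdrawn before the interview therefore lacks full ADE ascertainment and drops out of the primary model. The intention-to-treat sentence allows exceptions, and the follow-up restriction is one. Section 9.7 points towards inclusion but cannot supply data that were not collected. The 9.1a models for death and for emergency visit or readmission carry the same restriction, so even the data kept on withdrawn patients may go unused.

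**2. Which criteria can arise after exposure?**

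| Criterion (5.1.b) | Can arise after enrolment? |
|---|---|
| Short expected survival | Yes |
| Not reachable by telephone | Yes |
| Discharge from a non-study unit | Yes, by its own wording |
| Fewer than five usual home medications | Only on a literal reading; see the objection |

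**3. The plan's own target.** Section 9.2 gives 3 clusters, 4 periods and 500 per cluster-period, so 3 × 4 × 500 = 6000. The number needed to treat is 1/0.048 ≈ 21. The Hussey and Hughes variance is

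Var = Iσ²(σ² + Tτ²) / [(IU − W)σ² + (U² + ITU − TW − IV)τ²].

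Here I = 3, T = 4, U = 6, W = 14 and V = 14, so IU − W = 4 and U² + ITU − TW − IV = 36 + 72 − 56 − 42 = 10. Use the control-rate variance 0.15 × 0.85 = 0.1275 and an intracluster correlation of 0.03:

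- σ² = 0.1275 × 0.97/500 = 0.000247
- τ² = 0.1275 × 0.03 = 0.003825
- Var = 0.000294, SE = 0.01715
- 0.048/0.01715 − 1.96 = 0.84, so power is 79.9% (alpha taken as two-sided)

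At correlations of 0.01 and 0.05 the result is 79.9% and 80.6%. The stated 80% is reproduced. With the average-rate variance, power is 85.3–85.9%, and 5% uniform loss (475 per cell) lowers it only to 83.5–84.2%. Loss of precision is not the issue; selection is.

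**4. Size of the bias if there is no true effect.** Risk is 15% in both phases (9.2). The protocol gives no withdrawal rate, so every fraction below is an assumption. Intervention cells number 6 of 12, or 6 × 500 = 3000 patients, with 0.15 × 3000 = 450 expected ADEs.

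*(a) Withdrawn patients have twice the average risk (30%) and make up a share f of intervention patients.* Observed risk = (0.15 − 0.30f)/(1 − f).

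- f = 1% (30 patients): 0.147/0.99 = 14.85%, a spurious reduction of 0.15 points
- f = 5% (150 patients): 0.135/0.95 = 14.21%, a reduction of 0.8 points

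*(b) Only intervention patients with an ADE are withdrawn, in fraction w.* Observed risk = 0.15(1 − w)/(1 − 0.15w).

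| w | ADE patients withdrawn | Observed risk | Spurious reduction |
|---|---|---|---|
| 5% | 22.5 | 14.4% | 0.6 points |
| 10% | 45 | 13.7% | 1.3 points |
| 20% | 90 | 12.4% | 2.6 points |

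If 20% of ADE patients are withdrawn in the intervention phase and 5% in the control phase, the risks are 12.4% and 14.4%, a difference of 2.0 points. Equal fractions give no difference. If the control phase has the higher fraction, the sign reverses.

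**The case against.** The strongest reply is that the protocol leaves little room for outcome-driven withdrawal.

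- The primary outcome falls after discharge. Section 8.4 limits follow-up to the 30-day call, and 8.3 has adverse events otherwise collected and analysed at the end. The investigator will mostly learn of an ADE as it is recorded.
- Readmitted patients have a short-form interview at readmission (7.3), and deaths out of hospital are adjudicated after a next-of-kin interview (7.1).
- Palliative status is a planned subgroup and 30-day death an outcome (4.1), so patients near the end of life are evidently meant to be followed.
- Section 5.2 also requires that the new criterion preclude further participation, and neither a short prognosis nor an ADE prevents a telephone interview.

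Much of this stands. It makes the larger fractions in step 4(b) hard to defend and leaves 4(a), or something smaller, as the more credible case. It does not close the gap. Withdrawal in hospital, or between discharge and the call, remains permitted, and those routes to ascertainment are described for patients still in follow-up.

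Three stronger readings are tempting and are not supported.

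1. *A patient deprescribed below five drugs becomes withdrawable.* Section 2.6 ties the count to usual home medications at admission, and 7.1 compares the discharge prescription with the admission history. Stopping a drug in hospital does not change that history. Only a literal reading of 5.2 leaves this route open.
2. *An adverse event alone ends participation.* Section 5.2 also requires a best-interest or data-integrity judgement.
3. *The bias favours the intervention.* That follows only if withdrawal is more frequent among harmed patients in that phase. No figure in the protocol shows this.

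**Conclusion.** The point holds with moderate severity. Section 5.2 permits discretionary withdrawal, by someone who knows the phase, on criteria that can arise after exposure and on data-integrity grounds after an adverse event. Such withdrawal costs the ADE interview and, under 9.1a, a place in the primary model. It can bias both the ADE comparison and the withdrawal-event count.

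Neither the size nor the direction can be established from the protocol. Under the assumed fractions and no true effect, the distortion is about 0.15–0.8 points in the milder case and 0.6–2.6 points if only intervention patients with ADEs are lost, against a 4.8-point target. A reader might conclude that the primary result is invalid or that the rule must be changed before the trial can be interpreted. The protocol does not support that, since withdrawals may be few and balanced between phases.

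**What to change.** **Wording of section 5.2**

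- Delete *newly developed*.
- State that eligibility is judged once, from admission data, by the same rule in both phases. A later change in medication count, prognosis or reachability does not end study follow-up.
- Keep the best-interest provision. Add that an adverse event or ADE does not by itself end outcome follow-up and that, where the participant agrees, the 30-day interview is still done.
- Apply the discharge-unit exclusion in 5.1.b identically in both phases.

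This concerns study follow-up only and leaves clinical decisions and the team's freedom to act on the report as they are. It is a wording amendment with no new visits. The cost is the few planned interviews that withdrawal would otherwise have cancelled.

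**If conduct is complete.** Section 9.1b describes some analyses as already performed, so an amendment may come too late. In that case report investigator withdrawals by phase and reason. Add a sensitivity analysis that retains those patients, using the emergency-visit, hospitalization and vital-status data collected. Multiple imputation, which 9.5 already allows, is one way to do this for the ADE outcome. The cost is one table and one supplementary analysis.

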### *5.3 The type and timing of the data to be collected for withdrawn subjects.*

Vital status and hospitalization at 30-days post hospital discharge

### *5.4 Whether or how subjects are to be replaced:*

433 Not applicable

434

435 *5.5. The follow-up for subjects withdrawn:*

436

437 If they agree, a 2-minute phone call at 30-days post hospital discharge to determine if they  
438 visited the emergency department or were rehospitalized and to determine vital status.

439

440

## Section 6 – Treatment of Subjects

### *6.1 The intervention to be administered, including a description of the intervention, the timing, the method of administration, the follow-up period in the intervention and control arms*

The intervention consists of an electronically generated deprescribing report. A trained research assistant will collect the past medical history and certain lab values from the electronic chart and the medical admission note. They will enter this information along with the best possible medication history. The medication history will be elicited by a pharmacist or pharmacy technician. The information will be entered into the software MedSafer and a report will be generated based on cross-referencing with rules based on the existing evidence-based guidelines for deprescribing.

The report will only be generated after the medication reconciliation is performed by the pharmacist. In general, the report will be provided as soon as possible to the treating team and could be on day 0 or admission and up to day 3 of admission depending on resources on the unit and weekday or weekend admission status.

The team is free to act on the reports as per their local practice. At their own discretion, teams may choose to review reports at sign out, during rounds with pharmacists or prior to discharge.

Reports could be acted upon (or not) prior to hospital discharge. The discharge prescription is used as the final determination of whether deprescribing reports are acted on.

Participants who are taking sleeping pills or PPIs will also receive a brochure from the Canadian Deprescribing Network detailing the rationale for deprescribing this medication. All participants will receive a one-page study brochure that explains the rationale behind deprescribing which is available at <https://pamphlet.medsafer.org>

Participants will be phoned within and around 30-days post discharge (day 28-35) and they will have a structured interview to determine their current medication regimen and if it has changed, along with any contact (planned or unplanned) with the healthcare system, and any new or worsening conditions. They will also have the opportunity to report on their quality of sleep (Patient-Reported Outcomes Measurement Information System Sleep Disturbance Form 4a) and quality of life (EQ-5D-5L). All information will be collected in an electronic case file report for later blinded adjudication by an expert in pharmacy, geriatrics, or general internal medicine.

At the time of consent, we will also request access to provincial health insurance data up to one-year post hospital discharge in jurisdictions where available for use in subsequent analyses.

